## Abstract

**Background:**

There is a growing interest in developing tailored non-pharmacological strategies to face patients’ needs in dementia. Occupational therapy (OT) may contribute to promote self-empowerment of both patients and caregivers. France has implemented nationwide OT over a short-term period of 3/4 months. The main objective of the MathéoAlz study is to measure the impact of maintaining OT over 4 supplementary months on patients’ neuropsychiatric symptoms.

**Methods/design:**

The MatheoAlz trial (Maintenance of Occupational Therapy in Alzheimer’s disease) is a multi-center, pragmatic randomized controlled trial testing maintenance of OT over 4 supplementary months compared to routine OT delivered as recommended. This paper describes the study protocol. MatheoAlz plans to enroll 240 dyads, i.e. dementia patients and caregivers, whose main inclusion criteria are: prescription for routine OT, patients with mild or moderate dementia, living at home, receiving support from an informal caregiver. The study will compare a control group of patients benefiting from 12 to 15 initial sessions of OT over 3/4 months and an intervention group of patients benefiting from these initial sessions plus 8 extra home sessions over 4 supplementary months. The main outcome is the patient’s neuropsychiatric symptoms assessed by the Neuropsychiatric Inventory at 8 months. Several clinical outcomes and economic consequences are measured at 4, 8 and 12 months.

**Discussion:**

This is the first trial designed to assess the specific impact of the maintaining OT on the patients’ neuropsychiatric symptoms burden. The results will inform policymakers on strategies to implement in the near future.

**Trial registration:**

This trial was registered at ClinicalTrials.gov on February 16, 2018, identifier: NCT03435705.

## Background

About 6 million people are currently affected by dementia in Europe [1]. The majority of people with dementia live at home. Living in their own familiar environment may enable people with dementia to maintain their social networks and enjoy a better quality of life [2]. However, they experience a progressive cognitive and functional decline, limiting their ability to perform activities and to communicate; they also have frequent behavioral symptoms that are challenging for the caregivers and interfere with their daily functioning [3]. The progressive loss of social interactions contributes to reduce personal engagement in meaningful daily activities [4, 5]. Yet, engaging persons with dementia in personally-tailored activities may have positive effects on their challenging behaviors and quality of life. These benefits might positively influence caregivers’ burden and well-being. In France, a massive effort was made to optimize dementia care through a national Alzheimer plan 2008–2012 [6]. Several innovative health care services have been implemented nationwide, notably home services offering care plan based on occupational therapy (OT) model. OT allows tailored home support by cognitive and social rehabilitation for subjects with mild-to-moderate dementia; it aims to restore or mobilize the remaining abilities of individuals and adapt their domestic environment. The French OT model involves occupational therapists, psychomotor therapists and gerontologic assistants.

A growing interest in OT currently exists and some trials are ongoing [7, 8]. A review has concluded that literature provided a “proof of concept” that functional decline related to dementia may be delayed via OT interventions [9]. A 5-weeks OT’s program demonstrated clinical efficacy on daily functioning at 12 weeks in the Netherlands [10–12]. Nevertheless, the intervention’s replication in another national context failed to demonstrate any effectiveness [13]. Moreover, a recent US trial failed to demonstrate that OT added to collaborative care improves daily functioning over a 2-year period. It remains unclear whether results observed in efficacy trials with convenience and homogeneous samples are similarly obtained in routine care context. Participants who are typically volunteers for such trials differ from non-volunteers providing similar levels of care [14]. Yet, real-world studies are scarce. Recently, within an observational study based on routine care practice we showed that patients benefiting from OT experienced a stabilization in their functional performances over the 3/4 months intervention period before a worsening phase [15]. They also reported a decrease of their behavioral troubles followed by a stabilization phase. The French model of OT is a short-term intervention that enters into the intimacy of the daily functioning of patients and their caregivers, and the end of the intervention can be disruptive in a context of social and psychological frail equilibrium. Moreover, planning and implementation of relays (such as speech therapists, physiotherapists or personal care assistant) after OT are crucial to maintain therapeutic approaches according to patients’ care needs. Nevertheless, these tasks are time consuming and complex to accomplish in the devoted period. This report describes a protocol being used in an ongoing randomized trial aiming to provide evidence on long-term clinical effectiveness and economic consequences of maintaining OT over 4 extra months.

## Methods/design

### Aims and study hypothesis

The MatheoAlz trial (Maintenance of Occupational Therapy in Alzheimer’s disease) is a multi-center, pragmatic randomized controlled trial testing routine OT delivered as recommended compared to maintenance of OT over four supplementary months. After completion of the initial clinical assessment, participants are randomly allocated into the control group (treatment as usual with 12 to 15 home sessions over 3/4 months) or the treatment group (12 to 15 home sessions over 3/4 months + extra 8 sessions over 4 months). In order not to influence care practice and care organization in the control group, we decided to adopt a pragmatic approach. Thus, ESAs therapists provide routine care as usual in patients randomized in the control group. In this way, maintenance of OT will be compared to real-world care provided by ESAs therapists.

### Setting and participants

The study is being conducted in the South West of France; it began in 2018 and will run until 2019. Recruitment takes place through ESA (French acronym for “Equipe Spécialisée Alzheimer”) that are specialized teams of health professionals intervening at home for dementia patients. Patients are referred to ESA under medical prescription. We selected 10 ESA that were already involved in the pilot study (described elsewhere) and showed a high recruitment capacity [15]. Moreover, patients cared by these settings have been shown to be representative of the patients care by ESA at the national level [16]. All ESA staff met University research team for research compliance and human subject data collection. Eligibility criteria were pragmatically chosen to be representative of situations encountered by therapists in their routine care practice. Patients’ inclusion criteria include having a dementia diagnosis, being referred to an ESA for the first time, a MMSE score over 15, living in the community or in residential care setting and having a non-professional caregiver. Exclusion criteria are listed as follow: institutionalized patients or patients with a short-term project of institutionalization, patients with reported behavior of care refusal, patients already included in a non-pharmacological trial, patients under legal protective measures or not able to provide their written consent for participation in the study, patients or caregivers with characteristic that could affect participation (e.g.: major physical illness; sensory impairment; disability). People with dementia meeting the inclusion criteria will be recruited over an inclusion period of 10 months, this timeframe was estimated based on ESA’s inclusion capacity.

### Study procedures and randomization

Randomization will be performed with a 1:1 ratio, and will be stratified by territory nature (urban vs rural) and presence of gerontological coordination center in the area (yes vs no) in order to avoid imbalances on major characteristics that might influence care strategies and care effectiveness (see Fig. 1). Randomization process is centralized via a website accessible for each investigator allowing random allocation. Although patients cannot be blinded to their allocation treatment, all follow-ups assessments are gathered by assessors (psychologists) blinded to treatment allocation. Even if we cannot exclude that patients or/and caregivers inform inadvertently interviewers of the treatment they are receiving, we aim to reduce this hazard by giving explicit reminders to participants before randomization and by the use of self-measure whenever it is feasible.

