### Outcome measures

Primary and secondary measures are assessed after the initial planned intervention (first follow-up, M4), at 8 months (second follow-up M8) and at 12 months (third follow-up, M12). All outcomes and the timetable are shown in Table 1.

**Table 1 Tab1:** Overview of instruments (measures) in the MatheoAlz trial

		Inclusion	M4	M8	M12
MMSE		✓			
NPI		✓	✓	✓	✓
DAD		✓	✓	✓	✓
MADRS			✓	✓	✓
Apathy inventory			✓	✓	✓
Zarit			✓	✓	✓
RUD			✓	✓	✓
Sense of competence questionnaire			✓	✓	✓
Apathy Inventory			✓	✓	✓
QOLAD			✓	✓	✓

*MMSE*: Mini Mental State Examination

*NPI*: NeuroPsychiatric Inventory

*DAD*: Disability Assessment in Dementia

*MADRS*: Montgomery-Asberg Depression Rating Scale

*QOLAD*: Quality of Life in Dementia

*RUD*: Ressource Utilization in Dementia

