#### Secondary outcomes

b) Quality of life is measured using the Quality of Life-Alzheimer’s disease Scale (QOL-AD) [18]. The QOL-AD covers 13 domains of quality of life. It has good internal consistency, validity and reliability and its use is recommended by the European consensus on outcome measures for psychosocial interventions in dementia [19]. The scale presents high psychometrics properties whatever the dementia etiologies [20].

c) Functional performances are measured with the Disability Assessment in Dementia (DAD). This scale assesses 10 basic and instrumental activities of daily living and decomposed each activity into initiation, organization and efficacy. The sensitivity and reliability have been established [21].

d) Apathy is measured using the apathy inventory [22], that assesses emotional fatigue, initiative loss and interest loss. Psychometric properties are good [23].

e) Depression is assessed using Montgomery-Asberg Depression Rating Scale (MADRS) [24]. This scale explores 10 dimensions: apparent sadness, expressed sadness, inner tension, reduced sleep, reduced appetite, concentration difficulties, lassitude, inability to feel, pessimistic thoughts, suicidal thoughts. The MADRS is one of the most reliable scale to detect depressive symptoms in dementia population independently of the stage of severity [25].

f) Caregivers’ burden is assessed using the Zarit Burden Index (ZBI) [26]. The ZBI is a subjective measure of burden that includes 22 items exploring the caregiver’s perception and feelings about care situations.

g) Caregivers’ sense of competence is assessed with the sense of competence questionnaire [27].

h) Vital status and institutionalization and their dates are assessed at each follow-up using any sources of data available (main caregivers or the general practitioner).

i) Patients’ resource utilization is measured for the month prior to the visit using the Resource Use in Dementia (RUD) [28]. The RUD questionnaire was specifically designed to estimate formal resource utilization (primary and secondary care consultation, hospitalizations, social care services funded or brokered by local authorities…) as well as informal care for dementia-related activities. Primary caregivers are asked to notify the number of days and time spent for formal and informal caregiving activities provided during the month prior to the visit.

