j) Process of care in relation with dementia is assessed by asking caregivers for current use of anti-dementia drug, antidepressant drug, antipsychotic drug, consultation with a specialist (memory clinic, neurologist with private activity, psychiatrist, geriatrician) in the previous 3 months, speech therapist use, presence and type of home help support, financial subsidies support, and adult day care use.

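### Care-use questions at the follow-up visits may reveal the arm to the blinded assessors, and the stated safeguards do not cover this

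*Protocol article*

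**What the plan says.** Under Study procedures and randomization, the Protocol article concedes that patients cannot be blinded and relies on the interviewers instead: "all follow-ups assessments are gathered by assessors (psychologists) blinded to treatment allocation". The only hazard it names is accidental: "we cannot exclude that patients or/and caregivers inform inadvertently interviewers of the treatment they are receiving". Two measures are offered against it: explicit reminders to participants before randomization, and reducing the interviewer's role "by the use of self-measure whenever it is feasible".

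Under Outcome measures, Table 1 places both the NPI and the RUD at M4, M8 and M12. Under Secondary outcomes, item (i), "resource utilization is measured for the month prior to the visit using the Resource Use in Dementia (RUD"). The caregiver is the source of these data: "Primary caregivers are asked to notify the number of days and time spent for formal and informal caregiving activities provided during the month prior". Item (j) adds process-of-care questions put to caregivers, covering drugs, specialist consultations, "speech therapist use, presence and type of home help support, financial subsidies support, and adult day care use". Item (j) gives no visit times and does not appear in Table 1.

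Under Usual care, the control arm has 12 to 15 home sessions over 3/4 months. Under Intervention, the other arm has the same sessions and then 8 more over a further 4 months. Under Primary outcome measure, the NPI is administered as an interview, with each domain rated by the caregiver.

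**The concern.** The hazard that the protocol acknowledges differs from the one its schedule creates. A reminder not to mention the treatment can reduce stray remarks. It cannot stop a caregiver from answering truthfully when the trial asks which formal care was received in the last month. After the initial phase, only one arm has planned ESA home visits to report.

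The protocol's use of self-measurement could close this gap, but it is not assigned to the RUD or to the process-of-care items. Read literally, the claim that blinded psychologists gather all follow-up data includes both.

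Assessor blinding is the main masking measure in a trial where patients and caregivers know the arm. If the interviewer learns the arm before or during the NPI interview, expectation can enter through the probing. It could also enter other scales, so far as the psychologist scores them. An interviewer unmasked at one visit may carry that knowledge to the dyad's next visit.

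**Working it through.** **1. When arm-specific sessions fall inside a RUD window.** Inputs: initial phase of 3 or 4 months (Usual care, Intervention); 8 extra sessions over 4 months (Intervention); one-month recall (Secondary outcomes, item i); visits at M4, M8 and M12 (Table 1). Assumptions: months are counted from the start of the initial phase, and sessions are evenly spaced, so 8 / 4 = 2 per month.

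| Initial phase | Maintenance runs | M4 window (months 3–4) | M8 window (months 7–8) | M12 window (months 11–12) |
|---|---|---|---|---|
| 4 months | months 4–8 | no arm difference (both in initial phase) | about 2 sessions, intervention arm only | 0 |
| 3 months | months 3–7 | about 2 sessions, intervention arm only | 0 | 0 |

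On either nominal schedule, one window at or before the primary endpoint visit contains sessions that only the intervention arm receives. Which window it is depends on the length of the initial phase.

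**2. What the order of instruments changes.**
- 4-month initial phase: if the NPI at M8 is finished before service use is discussed, disclosure at that visit cannot affect the M8 NPI. It could carry to M12.
- 3-month initial phase: disclosure could occur at M4. Taking the NPI before the RUD at M8 then gives no protection if the same psychologist returns.

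**3. The sample size, which this point leaves unchanged.** The figures 14 and 11 under Sample size are labelled standard errors but work only as standard deviations. Per arm, n = (1.960 + 0.842)² × (14² + 11²) / 5² = 7.85 × 317 / 25 = 99.5, so 100. With 15% attrition, 100 / 0.85 = 117.6, so 118 per arm and 236 in total, against the stated 240.

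**4. Illustration of scale only.** With 240 randomized 1:1 and 15% lost, 120 × 0.85 = 102 per arm are evaluable. SE = √(317 / 102) = 1.763. If there is no true effect but ratings are shifted by b points, the two-sided error at nominal 5% is 1 − Φ(1.96 − b/1.763) + Φ(−1.96 − b/1.763).
- b = 1: b/SE = 0.567, error 0.088.
- b = 2: b/SE = 1.134, error 0.206.

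The values of b are assumed; the document gives no size for interviewer bias. The figures show what any shift of that size would do and are not evidence that one will occur.

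**The case against.** A reader might infer that the psychologists must ask these questions themselves, and that the questionnaires therefore unmask them at the primary endpoint visit. The document does not support that, for these reasons:

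- **Mode of collection.** The RUD text does not say whether it is an interview or a form. A caregiver-completed RUD is compatible with it and with the stated preference for self-measurement.
- **Content.** ESA or occupational therapy sessions are not named in item (i) or item (j). The Economic evaluation section costs the extra sessions as a separate programme item, so the economic analysis does not visibly need caregivers to report them.
- **Timing.** After a 3-month initial phase, the M8 window may hold no planned session.
- **Order and staffing.** The article does not give the order of instruments or say whether an assessor returns to the same dyad. An article commonly leaves such detail to the full protocol, so its absence is no fault in itself.
- **Route to the primary outcome.** The caregiver, who knows the arm, rates each NPI domain. An unmasked interviewer can act only through the probing. The document does not say who scores the MADRS or the apathy inventory.
- **Candour.** The protocol openly admits that blinding may fail.

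All of this stands, and it limits the point to a risk. It does not remove it. The list of formal care in item (i) is open-ended, item (j) asks about type of home help, and a caregiver who receives home visits may well report them under either. The point rests on what the article states: blinding claimed for all follow-up data, care-use questions within that follow-up, and reminders aimed at a different kind of disclosure.

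**Conclusion.** The point holds as a foreseeable risk to assessor blinding. Truthful answers to care-use questions are likely to reveal the arm in some intervention dyads, at M8 or at M4 according to the length of the initial phase. The reminders cannot prevent this, and self-measurement is not assigned to the items where it would help most.

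The number of dyads affected and any resulting bias cannot be derived from the document. The effect on the NPI is limited by the unblinded caregiver's role as rater. The error rates of about 9% and 21% depend wholly on assumed shifts of 1 and 2 NPI points. The conclusion assumes evenly spaced sessions, visit months counted from the start of the initial phase, and caregivers who count ESA visits as formal care or home support. No sample-size figure changes. Because the remedy costs so little, the change is worth making.

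**What to change.** At every follow-up visit:

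1. Complete and lock the NPI, and then the other rated scales (MADRS, apathy inventory, DAD, QOL-AD), before any question on service use.
2. Collect the RUD and process-of-care items on a caregiver-completed form that the assessor does not see, or ask them last.
3. If they are asked last, have a different psychologist from the existing team do the dyad's next visit where feasible (M4 to M8, and M8 to M12).
4. Record the assessor's guess of the arm immediately after the NPI, so that the success of blinding can be reported.

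The section on Study procedures and randomization should then say that disclosure through the trial's own questions is handled by these steps, alongside the reminders.

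Cost: the order of the case report form, a short assessor instruction and some scheduling. No extra visit, staff or participants are needed. A self-completed RUD may have slightly more missing items.

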**Fig. 1 Fig1:**
[figure not shown]
Flowchart of study design

Consent for participating to the study was signed by each participant after they received a full explanation in person, with the opportunity to ask questions to therapists. All participants have the right to decline participation or withdraw from the study at any time without giving a reason. The study protocol, information brochure and informed consent procedure were approved by the medical ethics committee for Human (Comité de protection des personnes d’Ile de France 1, 6th November 2017) and the study was registered in clinical trial (NCT03435705).

### Usual care

The participants allocated to the control group benefit from the usual intervention described previously [15]. Briefly, patients referred to ESA followed a standardized treatment procedure consisting of 12 to 15 home sessions performed by a therapist over a period of 3/4 months focusing on patients and potential primary caregivers. The initial assessment (1 or 2 sessions) allows the therapist to evaluate remaining abilities, and to define patients’ and caregivers’ expectations and needs. In the following sessions, patients were taught to optimize compensatory and environmental strategies to improve their performance in daily activities. Through demonstration with patients, primary caregivers were trained to use effective supervision, problem solving, manage situational distress and coping strategies to sustain patients’ social participation. Caregivers also learned to simplify activities for future decline and how to use strategies to other daily care challenges. At the end, few sessions could be devoted, according to patients and caregivers’ expectations and needs, to initiate and prepare home care support following the initial OT intervention.

### Intervention

As described above, providing meaningful and tailored activities according to patients and caregivers’ expectations and needs is the core of OT. The therapeutic approach includes environmental modifications, behavior management, physical activity, and emotional support as active components. As for the control group, the intervention group will have a first period of 3/4 months consisting of 12 to 15 home sessions; after this period the intervention group will have a maintenance of OT over 4 supplementary months with 8 extra sessions. This maintenance of OT over a longer period aims to optimize therapeutic approaches implemented during the initial 12/15 sessions by 1°) reinforcing caregivers’ confidence and competency and 2°) allowing a better matching between individual needs and further home care support.

### Outcome measures

Primary and secondary measures are assessed after the initial planned intervention (first follow-up, M4), at 8 months (second follow-up M8) and at 12 months (third follow-up, M12). All outcomes and the timetable are shown in Table 1.

**Table 1 Tab1:** Overview of instruments (measures) in the MatheoAlz trial

		Inclusion	M4	M8	M12
MMSE		✓			
NPI		✓	✓	✓	✓
DAD		✓	✓	✓	✓
MADRS			✓	✓	✓
Apathy inventory			✓	✓	✓
Zarit			✓	✓	✓
RUD			✓	✓	✓
Sense of competence questionnaire			✓	✓	✓
Apathy Inventory			✓	✓	✓
QOLAD			✓	✓	✓

*MMSE*: Mini Mental State Examination

*NPI*: NeuroPsychiatric Inventory

*DAD*: Disability Assessment in Dementia

*MADRS*: Montgomery-Asberg Depression Rating Scale

*QOLAD*: Quality of Life in Dementia

*RUD*: Ressource Utilization in Dementia

